#### 5.9 Pharmacokinetic analysis:

On each series of drug plasma concentrations, the following pharmacokinetic parameters will be determined, using the software package WinNonLin (Pharsight Corporation, California).

- Area under the curve for plasma concentration vs. time, until the last sampling time after dosing (AUCt)

- Peak plasma concentration ( $C_{\max}$ )
- The trough plasma concentration at the last time of sampling, immediately before the next dose.
- Time to peak plasma concentration ( $T_{\max}$ ).
- Half-life ( $T_{1/2}$ ).

The PK measures will be summarized using parametric or nonparametric methods (as appropriate). For RBT, the results from PK1 will be compared to PK2 and PK3, respectively. PK2 and 3 will be compared for all the drugs. The significance of differences between the pharmacokinetic measures will be determined using the Student t-test (parametric data) and the Wilcoxon signed rank test (nonparametric data). Bioequivalence analysis will be conducted using ANOVA for the AUC and  $C_{\max}$  values. The geometric mean ratios and their 90% confidence intervals will be reported. In addition the inter-individual and intra-individual variability will be evaluated for the PK measures. No interim PK analyses are planned. In addition, potential polymorphisms in specific enzymes involved in drug metabolism will be investigated.

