### Treatments of the Trial:

Patients will have Rifampin replaced by Rifabutin 300mg once a day (OD) during the first two weeks of intensive phase of tuberculosis treatment. After two weeks, the first PK study (PK1) will be completed. Patients will then be randomized to receive a combination of RBT and ARV, with different doses of RBT:

- A: NRTI + LPV/r (2 tabs twice a day) + RBT (150 mg TPW);
- B: NRTI + LPV/r (2 tabs twice a day) + RBT (150 mg OD)

Half the patients will be allocated to sub-treatment (A) and then switched to treatment (B) after three weeks, and half will be allocated the reverse (B then A). PK2 takes place three weeks after PK1 and PK3 three weeks after PK2, at the end of the intensive phase

After the PK3, during the continuous phase of tuberculosis treatment, participants will be referred to National Tuberculosis Program and to National AIDS Program to be treated according to standard care. Rifabutin will be switched to rifampicin and lopinavir/rtv to efavirenz. Thus patients will be treated and followed according to recommendations from and by the National TB Program and by the National AIDS program. An end study visit will be done at the end of the TB treatment between W24 and W26.

End-points: The bioavailability of RBT will be measured by the  $AUC_{0-24}$  and compared to the  $AUC_{0-24}$  for each of the RBT doses in combination with the ARV. In addition, the bioavailability of the LPV in combination with two doses of RBT will be determined by the  $AUC_{0-12}$ .

Sample size: 32 patients

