### **2.2 Secondary objectives:**

1. To compare the bioavailability of two different doses of RBT in combination with LPV/r, with the bioavailability of RBT taken without ART in Vietnamese HIV infected patients with pulmonary tuberculosis and advanced immunodeficiency.
2. To determine the bioavailability of LPV/r in combination with RBT in Vietnamese TB patients with advanced immunodeficiency.
3. To determine the outcomes of tuberculosis treatment with rifabutin 150 mg once per day or thrice per week in combination with LPV/r during the initial phase of tuberculosis treatment.
4. To determine the safety and toxicity of RBT in combination with ART during the initial phase of tuberculosis therapy in Vietnamese patients.
5. To assess the genetic differences that may affect the response to antiretroviral and tuberculosis treatments.

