### **3. Outcome measures:**

#### **3.1 Primary outcomes:**

The primary study objective is to compare the pharmacokinetics of two different doses of RBT in combination with LPV/r, with the pharmacokinetics of RBT taken without ART in HIV infected patients with pulmonary TB and advanced immunodeficiency. The pharmacokinetics of RBT without ARV will be measured by the area under the curve ( $AUC_{0-24}$ ), and compared to the  $AUC_{0-24}$  for each of the RBT doses in combination with the ARV (and  $AUC_{0-48}$  in case of the three times weekly LPV/r arm).

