### **4. Sample size:**

Based on the  $AUC_{0-24}$  for RBT determined in previous studies (19) it was estimated that a sample size of 12 participants has a power of 80% to detect a 20% difference between the mean  $AUC_{0-24}$  for the participants taking RBT without ARV and the  $AUC_{0-24}$  for RBT combined with the various ARV. To provide a target of 12 evaluable patients in each arm (24 patients in total), because patients with low CD4 counts liable to be recruited into this study may have high mortality and morbidity, resulting in a high attrition rate, we propose a maximum of 32 patients may be enrolled (16 per arm). These additional subjects will allow a comparison of pharmacokinetic parameters between patients initiating high dose RBT with those initiating low dose RBT, and sufficient power to detect any sequence effect.

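### Section 5.9 defines its rifabutin and lopinavir comparisons by PK visit, but sections 2.2 and 3.1 ask for comparisons by rifabutin dose, and in this cross-over PK2 and PK3 each contain both doses

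*Protocol*

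**What the plan says.** Section 5.9 lists the comparisons: "For RBT, the results from PK1 will be compared to PK2 and PK3, respectively. PK2 and 3 will be compared for all the drugs". Significance is to be judged by Student t-test or Wilcoxon signed rank test. A separate sentence follows: "Bioequivalence analysis will be conducted using ANOVA for the AUC" and Cmax values, with geometric mean ratios and 90% confidence intervals to be reported. No factor or contrast is given for that ANOVA. Section 5.9 does not mention dose, arm, sequence or period.

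The design is in the Detailed Summary (Treatments of the Trial): "Half the patients will be allocated to sub-treatment (A) and then switched to treatment (B) after three weeks, and half will be allocated the reverse". Regimen A is 150 mg TPW and regimen B is 150 mg OD, both with LPV/r. Section 2.1 repeats the scheme, with 16 patients starting on each.

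The question is by dose. Section 3.1 compares the AUC of rifabutin without ARVs with the AUC "for each of the RBT doses in combination with the ARV". Secondary objective 1 in section 2.2 reads: "To compare the bioavailability of two different doses of RBT in combination with LPV/r, with the bioavailability of RBT taken without ART". Section 4 adds that the enrolled number should give power to detect a sequence effect.

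**The concern.** A visit label identifies a dose only when everyone takes the same dose at that visit. That is true of PK1 (300 mg alone). It is not true of PK2 or PK3, where the doses are swapped between arms. The comparisons tied to the named tests therefore do not match the contrast in the primary outcome.

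The Background gives the trial's purpose as dose selection for a phase III trial. If the visit comparisons were run on all patients together, one dose that under-exposes and another that over-exposes could average to no difference from 300 mg alone. Lopinavir is the most exposed: Table 3 has it assayed only at PK2 and PK3, so PK2 versus PK3 is its only comparison.

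**Working it through.** **The plan's own figure.** Section 4 says that "a sample size of 12 participants has a power of 80% to detect a 20% difference". Neither the SD nor alpha is given, so the figure can only be back-solved. At two-sided 0.05 and 80% power, n = 12 implies an SD of the paired difference of 22.5% of the mean (within-patient CV about 16%). With a two-sample test it implies an SD of 16.7%. The point below does not depend on this; 16% serves only as the low end of an assumed CV range, with 30% as the high end.

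**Set-up.** On the log scale, let A and B be the mean log exposure on TPW and OD, d = B − A, and p the period effect (PK3 minus PK2).

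| | PK2 | PK3 | PK3 − PK2 |
|---|---|---|---|
| Sequence A then B | A | B + p | d + p |
| Sequence B then A | B | A + p | −d + p |

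**Reading 1: visits pooled across arms.**

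- Equal numbers: the mean of PK3 − PK2 is [(d + p) + (−d + p)]/2 = p. The dose effect cancels.
- Unequal numbers, 14 and 10: the mean is p + d(14 − 10)/24 = p + d/6. With OD/TPW = 2.0 and p = 0 the ratio is 2^(1/6) = 1.12.
- PK2 − PK1 averages to (A + B)/2 − PK1. PK3 − PK1 averages to the same plus p. If TPW equals PK1 and OD is twice PK1, each ratio is √(1.0 × 2.0) = 1.41 (with p = 0). If the true ratios to PK1 are 0.7 and 1.4, each is √(0.7 × 1.4) = 0.99.
- The +d/−d split also inflates the SD of the differences. At CV 30% the within-patient log-SD is √ln(1.09) = 0.294, so the SD of a difference is 0.294 × √2 = 0.415. With d = ln 2 = 0.693 and 24 patients, the pooled SD is √(0.415² + 0.693² × 24/23) = 0.821.

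Simulation (20,000 trials, 12 + 12 patients, no period effect, two-sided 0.05, CV 30%):

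| True OD/TPW | Pooled PK3/PK2: ratio, rejection | By dose: ratio, rejection |
|---|---|---|
| 1.5 | 1.00, under 1% | 1.5, over 99% |
| 2.0 | 1.00, about 0.02% | 2.0, 100% |

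At a log-SD of 0.16 the pooled rejection rate is about 0% for both ratios, and the by-dose rate is 100%.

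**Reading 2: visits compared within arm.** The dose effect remains but carries p. With OD/TPW = 2.0 and an assumed period ratio of 1.2:

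- Arm A: PK3/PK2 = 2.0 × 1.2 = 2.40.
- Arm B: PK3/PK2 = 0.5 × 1.2 = 0.60, that is OD/TPW = 1/0.60 = 1.67.
- Combining both sequences by dose removes p: √(2.40 × 1.67) = 2.00.

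**Precision of OD versus TPW.** 90% CI factor = exp(t × SE), at CV 30%:

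- By dose, 24 patients: SE = 0.415/√24 = 0.0847, t(22) = 1.717, factor 1.16.
- Within arm, 12 patients: SE = 0.415/√12 = 0.120, t(11) = 1.796, factor 1.24.
- Pooled by visit at a true ratio of 2.0: SE = 0.821/√24 = 0.168, t(23) = 1.714, factor 1.33. This interval surrounds the wrong quantity.

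**The case against.** Section 5.9 never says that visits are pooled across arms, and other text points away from pooling. Section 3.1 fixes the primary contrast by dose. Table 3 splits PK2 and PK3 into arm A and arm B columns. Section 4 bases power on 12 participants and targets 12 evaluable patients in each arm, which fits comparisons within arm; pooling by visit would use 24. Within arm A, PK1 versus PK2 and PK1 versus PK3 are the two dose contrasts that section 3.1 wants, and nothing cancels. The ANOVA with geometric mean ratios may be intended as the dose analysis, and its model terms are properly left to an analysis plan.

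Most of this stands. A reader might infer that section 5.9 makes the primary question unanswerable, or that PK2 versus PK3 is zero by construction. The documents do not support either. The within-arm reading is open, the ANOVA contrast is unstated rather than wrong, and even under pooling the contrast estimates the period effect, with exact cancellation of dose only when the sequences have equal evaluable numbers. A reader might also infer that sequence is ignored altogether, but section 4 does contemplate it.

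What does not stand is that this removes the problem. Section 5.9 does specify comparisons, and their labels do not match section 3.1. The within-arm reading gives up the protection against period effects that randomising the order provides, and half the patients. An ANOVA with no stated factor cannot decide between the readings.

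**Conclusion.** The point holds as a mismatch between section 5.9 and sections 2.2 and 3.1. On either available reading, the named tests do worse than the design allows. Pooled, the dose effect cancels or nearly cancels from PK2 versus PK3, and the contrasts with PK1 are averages over the two doses. Within arm, OD versus TPW is mixed with period and rests on about 12 patients instead of 24.

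The cancellation and the confounding are algebraic and need no assumed SD. The simulated rejection rates and the factor of 1.33 apply to the pooled reading only. They rest on an assumed CV and assumed dose ratios, and the 2.40 and 1.67 rest on an assumed period ratio of 1.2. The intended contrast is clear from section 3.1, so a careful analyst would probably regroup by dose. It is better to write that down before the data are seen.

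**What to change.** In section 5.9, replace the two sentences on visit comparisons with text stating that:

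- PK2 and PK3 data are regrouped by the rifabutin regimen taken at that visit;
- log AUC and log Cmax are analysed with regimen and patient in the model, adding sequence and period terms for OD versus TPW;
- geometric mean ratios with 90% confidence intervals are given for TPW/PK1, OD/PK1 and OD/TPW;
- lopinavir is compared by concurrent rifabutin dose in the same way.

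Add one sentence acknowledging that PK1 is always the first period, so contrasts with PK1 remain confounded with time however the data are grouped. For example, a PK3/PK2 period ratio of 1.2 shifts each dose's balanced ratio to PK1 by √1.2 = 1.10.

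The choice between ANOVA and a mixed model, and the role of the t-test and Wilcoxon test, can be left to the analysis plan. The cost is wording only: no new patients, samples or assays.

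### Section 5.9 picks a t-test or signed rank test by how the data look but reports geometric mean ratios, so P value and interval for one contrast can come from different analyses and disagree

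*Protocol*

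**What the plan says.** Section 5.9 of the protocol lists AUC, Cmax, trough, Tmax and half-life, and then gives three instructions that bear on one comparison.

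- Summaries: "The PK measures will be summarized using parametric or nonparametric methods (as appropriate").
- Tests: significance "will be determined using the Student t-test (parametric data) and the Wilcoxon signed rank test (nonparametric data").
- Effect size: "Bioequivalence analysis will be conducted using ANOVA for the AUC and" Cmax, followed by "The geometric mean ratios and their 90% confidence intervals will be reported".

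The contrasts are within patient: "For RBT, the results from PK1 will be compared to PK2 and PK3, respectively", and PK2 is also compared with PK3. Section 4 states its effect size as a relative difference in means: 12 participants are said to give a sample that "has a power of 80% to detect a 20% difference between the mean" AUC values. Neither section gives an alpha, a scale for the tests, or a rule for when data count as parametric.

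**The concern.** The test sentence is an instruction, so this is more than a detail left for later. Read plainly, each measure goes to one test or the other according to how its values look, and the same values are then tested. Neither test is tied to the analysis that produces the geometric mean ratio.

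On raw values the three procedures have three targets: the t-test a difference in arithmetic means, the signed rank test the centre of the paired raw differences, and the interval a ratio of geometric means. One contrast could then carry a P value that contradicts its own interval, with the choice of test still open once the data are seen. Comparing each rifabutin dose given with LPV/r against rifabutin alone is the primary outcome (Section 3.1), so these are the contrasts affected. Raw-scale tests of skewed exposure data also tend to have less power than a log-scale test.

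**Working it through.** **Inputs from the protocol.** n = 12, power 80% and a 20% difference (Section 4); a target of 24 evaluable patients and a maximum of 32 (Section 4); geometric mean ratio (GMR) with 90% CI (Section 5.9).

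**Not in the protocol, so assumed.** Two-sided 5%; log-normal AUC; the between-patient and within-patient spreads below; the t-test taken as paired, like the signed rank test; both tests on raw values; selection by Shapiro-Wilk at 5% on the paired differences.

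**Step 1. The plan's own figure.** "sample size of 12 participants has a power of 80% to detect a 20% difference between the mean" AUC values cannot be reproduced, because no SD or alpha is given. It can only be solved backwards.

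- Raw scale, normal formula: SD of the paired difference = 0.20 × √12 / (1.960 + 0.842) = 0.247 of the mean. With the t distribution it is 0.225.
- Log scale for a ratio of 0.80, t distribution: 0.251. Within-patient log SD = 0.251/√2 = 0.178, a CV of about 18%.

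So 12 is attainable, but it does not show which scale was meant.

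**Step 2. Power at 24 pairs, equal spread.** ln AUC = patient effect + ln(GMR) + visit error. The rule (Shapiro-Wilk, then raw paired t or signed rank) is set against a paired t-test on ln AUC.

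| Between / within log SD | GMR 0.80: rule vs log | GMR 1.25: rule vs log |
|---|---|---|
| 0.35 / 0.25 | 81% vs 85% | 80% vs 84% |
| 0.50 / 0.25 | 78% vs 85% | 77% vs 84% |
| 0.60 / 0.30 | 61% vs 70% | 60% vs 69% |

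The loss is 4, 7 and 9 points in each direction. A repeat run for GMR 0.80 gave 79/79/61% against 83/84/69%, a loss of 4, 5 and 8 points. In that run the two tests disagreed on P<0.05 in 7% to 15% of trials.

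**Step 3. A wider range, and where the disagreement comes from** (24 pairs, GMR 0.80, figures in %). The last column is the share of trials in which the 90% interval excludes 1, minus the log-scale power (for example 91.7 − 85.3 = 6.4).

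| Within / between CV | Rule power | Log power | Loss | Rule (5%) vs 90% interval | Rule (5%) vs 95% interval | Log test (5%) vs 90% interval |
|---|---|---|---|---|---|---|
| 17 / 30 | 98.7 | 99.4 | 0.7 | 1.0 | 0.8 | 0.3 |
| 17 / 60 | 97.8 | 99.2 | 1.4 | 2.0 | 1.5 | 0.6 |
| 25 / 30 | 81.8 | 84.7 | 2.9 | 10.2 | 6.7 | 6.8 |
| 25 / 60 | 78.3 | 85.3 | 7.0 | 14.1 | 10.9 | 6.4 |
| 35 / 30 | 54.9 | 58.7 | 3.8 | 17.9 | 9.9 | 13.3 |
| 35 / 60 | 51.3 | 59.3 | 8.0 | 21.8 | 14.4 | 12.3 |

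The last three columns are percentages of trials that disagree. Part of the mismatch is only a 5% test set beside a 90% interval, since it appears even when both are on the log scale. A further part remains against a 95% interval, and that part comes from the different analyses. At n = 12 the same three columns run 10–23%, 6–14% and 7–15%.

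**Step 4. Type I error.** At GMR 1 with equal spread and 24 pairs, the rule rejects in 4.9% to 5.1% of trials. Over n = 12, 24 and 32 it never exceeds 5.4%.

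**Step 5. Unequal spread.** With between-patient log SD 0.35 and within-patient log SD rising from 0.20 without LPV/r to 0.45 with it, power for GMR 0.80 is 37% under the rule against 57% on the log scale. For GMR 1.25 it is 67% against 57%. Reverse the spread (0.45 to 0.20) and the fall is favoured: 66% under the rule against 57%. The raw tests move because arithmetic means differ even at GMR 1: exp((0.45² − 0.20²)/2) = 1.085. Rejection at GMR 1 is then about 6% to 7%.

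**The case against.** Section 5.9 never says that the tests use raw values. The neighbouring sentences on ANOVA and geometric mean ratios imply logs, and a statistical analysis plan could say so. If the t-test were on log AUC, most of the power loss would go whenever that test is used. The two data labels could also mean the type of measure, with Tmax sent to the signed rank test, and no Shapiro-Wilk step is written. Finally, no dose decision is tied to P<0.05, and a bioequivalence interval and a difference test answer different questions.

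Much of this stands. The raw scale is the natural reading, since logs are not mentioned and the stated response to unsuitable data is another test, but it remains an inference. The pre-test and all SDs are assumptions. What the objection does not remove is that the text sends significance and effect size down separate routes, and a later plan would have to override that sentence as well as add detail.

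A reader might go further and infer that the rule specifically hides a fall in rifabutin exposure, and link that to the acquired rifamycin resistance discussed in Section 2.3. The documents do not support this. At equal spread the loss is the same for a fall and its mirror-image rise. With unequal spread the favoured direction depends on which visit is more variable, and the protocol says nothing about that. Section 2.3 reports large increases in rifabutin AUC with LPV/r, and the net effect at the reduced doses is open.

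**Conclusion.** The concern holds in a limited form. Section 5.9 lets the P value and the geometric mean ratio interval for one contrast come from different analyses, and they can disagree. If the tests are on raw values, power at 24 pairs for a ratio of 0.80 or 1.25 falls by roughly 4 to 9 points under the assumed log SDs, and by about 1 point where variability is low. Power is reduced, not lost. Type I error stays near 5% at equal spread, so the cost is coherence and some efficiency, and a reader should not infer inflated false positives. Nor should all the disagreement be put down to the choice of test, because part of it is the 5% test beside a 90% interval. The point is modest in size but worth correcting, since it concerns the primary contrasts.

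**What to change.** Replace the test-selection sentence in Section 5.9 as follows.

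- Analyse AUC, Cmax and trough as natural logarithms in one within-patient model. Take the geometric mean ratio, its interval and the P value from that model.
- State the confidence level and the test level so that they match. Otherwise say that the 90% interval serves the bioequivalence question and that the test is read against a 95% interval. Without this, the level mismatch in Step 3 remains.
- Do not select the test by inspecting normality. Keep the signed rank test for Tmax and as a sensitivity analysis. Arithmetic means and medians stay as descriptive summaries.

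The cost is a few sentences in Section 5.9 or the analysis plan, with no new patients, samples or assays. The planned geometric mean ratios already imply the log-scale model. The one downside is that raw-scale P values are no longer the main test.

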#### 5.10 Pharmacogenomics samples

DNA analysis will be performed on whole blood in order to determine the polymorphisms of the cytochrome P450 and other genetic loci implicated in drug metabolism. These analyses will be carried out by the Pharmacology Unit of Hospital Kremlin-Bicêtre in Paris in collaboration with other laboratories where necessary. Techniques for agnostic screening of genome wide loci using microarrays, automated DNA sequencing or other technologies may also be deployed. Shipment of samples will be the responsibility of Pasteur Institute, Ho Chi Minh City and the Pharmacology Unit of Hospital Kremlin-Bicêtre in Paris.

#### 5.11 Storage of samples

Aliquots of plasma will be stored at -80 degrees in the Department of Biological Analysis at Pasteur Institute, HCMC. Microbiological samples will be stored in the Department of Microbiology at Pham Ngoc Thach Hospital for 2 years.

All efforts will be made in order to upgrade the Pasteur Institute laboratory to perform the pharmacokinetics analysis of lopinavir/ritonavir, and rifabutin/metabolite. This will be done through appropriate training and transfer of technology. Human and non human samples will be exchanged between the Pharmacology Unit at University Hospital Kremlin-Bicêtre in Paris (France) and Pasteur Institute in Ho Chi Minh City, to perform the necessary quality controls. If, for exceptional and unpredictable reasons, Pasteur Institute is unable to carry out the PK analyses by the end of follow-up

of the last patient included in the study, plasma samples will be transferred to the Pharmacology Unit of Hospital Kremlin-Bicêtre in Paris in order to perform the pharmacokinetics analyses.

#### 5.12 Provisional dates:

|                                                     |                  |
|-----------------------------------------------------|------------------|
| Submission to authorities:                          | 15 April 2008    |
| Full approval received:                             | 23 March 2009    |
| Approval Vietnamese Ministry of Health:             | 13 October 2008  |
| Re-approval Vietnamese Ministry of Health:          | 21 April 2010    |
| Start recruitment:                                  | 25 June 2010     |
| Enrolment interruption:                             | 19 October 2010  |
| Submission protocol version 4. 2:                   | 20 April 2011    |
| Expected approval by Vietnamese Ministry of Health: | 15 June 2011     |
| Start enrolment:                                    | 15 August 2011   |
| Finish enrolment:                                   | 15 February 2012 |
| Complete follow-up:                                 | 15 August 2012   |
| Complete analysis and reporting:                    | 15 November 2012 |

